## Discussion

Worldwide, a significant number of people experience the disappearance of a loved one. Surprisingly, no RCT has ever been conducted to systematically evaluate the effectiveness of a psychological treatment for persistent psychopathology among relatives of missing persons. Knowledge about treatment effects is needed to improve treatment options for those in need of help. This article describes the rationale and methods of a multi-centre pilot RCT focused on the evaluation of the feasibility and preliminary effectiveness of CBT with elements of mindfulness for relatives of missing persons. The treatment is based on CBT for bereavement-related psychopathology and aims to reduce dysfunctional cognitions and avoidance behaviour. Elements of mindfulness are added to the therapy to enhance skills to tolerate the ambiguity surrounding the disappearance and to prevent participants becoming entangled in negative thoughts.

Strengths of this study are (1) the development of a treatment that is targeted to a specific population, (2) the evaluation of the possible mechanisms of change of the treatment, (3) the inclusion of both an intervention and waiting list control group, (4) the use of a pilot design before exposing a large sample to a treatment that has yet to be evaluated, (5) the assessment of eligibility not only by self-report questionnaires but also with a clinical interview, and (6) the monitoring at micro-level of potential change mechanisms of the treatment. One of the limitations of this study is the lack of power to conduct a multilevel analysis to take into account the nested structure of the data (i.e., repeated measures, nested in individuals, who are, in turn, nested in families or other social systems associated with the same missing person). In addition, the recruitment procedures are focused on a non-treatment seeking population. The percentages of individuals who are willing to participate might therefore be relatively low compared to other studies, and the recruitment of sufficient numbers of participants might therefore be a challenge. Moreover, treatment fidelity will be monitored by methods that rely on self-report which might be prone to bias. Finally, participants whose loved one disappeared less than 12 months earlier can formally not fulfil the criteria of PCBD, because one of the proposed criteria of PCBD is that at least 12 months has elapsed since the loss. The reason for this time frame is to distinguish normal from pathological grief [14]. Because little is known about the grief reactions following the disappearance of a loved one, a shorter time frame is chosen to offer support for those in need of help.

As a result of this pilot study, we may have some evidence whether CBT is effective for relatives of missing persons. Since this is a pilot study, the future results of this study need to be interpreted with caution. The recommendations for the execution of a large-scale RCT based on the results of this pilot study are expected to be relevant for future research. Future intervention studies should verify the results of this study and other possibly effective treatments in order to offer an evidence-based intervention for this population. Taken together, this study will provide the first results of a pilot RCT that evaluates the potential effectiveness of CBT for relatives of missing persons suffering from psychopathology.

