### Recruitment of participants

All recruitment procedures aim to enrol individuals of whom a loved one has been missing for participation in a survey study. The survey study aims to explore the psychological consequences for relatives of missing persons. The survey study and pilot RCT are both part of the same research project. We will recruit participants through several pathways. Firstly, representatives from a television show focused on the search of missing persons and a peer support group will distribute invitation letters to relatives of missing persons. Secondly, Victim Support the Netherlands, a governmental organisation in which professionals, mostly social workers, offer practical and legal support to victims, will inform potential participants about the research project. Thirdly, other participants will be recruited via announcements in the media, presentations at meetings for relatives of missing persons, and snowball sampling (each participant is asked to invite others). After signing up for the survey study, the participants will be sent a questionnaire including an information letter and informed consent form for participation in the survey study. The letter informs participants about the aims of the survey study and the possibility to participate in a subsequent study designed to evaluate a psychological intervention specifically developed for relatives of missing persons.

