Randomisation will take place after the participant is screened for eligibility based on the M.I.N.I. Plus and the TGI. A random number generator will be used to perform the blocking randomisation procedure. Relatives of the same missing person will be allocated to the same study arm (i.e., intervention or waiting list condition), in order to prevent transfer of information. An independent researcher will conduct the randomisation procedure. Neither the participants nor the researchers will be blinded. The M.I.N.I. Plus and the Traumatic Grief Interview will be conducted again after the treatment, to examine whether numbers of cases of PCBD, MDD, and PTSD have decreased. The researchers will reimburse costs related to the treatment that are not covered by the respondents’ health insurance. Travel expenses that are related to the visits to the therapist will also be reimbursed (see Fig. 1 for a flowchart of the procedures).

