##### Data analyses

Within-subjects repeated measures ANOVA with time (baseline, 1, 12, and 24 weeks post-treatment) as the repeated measure will be performed to evaluate the effects of the treatment in terms of changes in mean scores of PCBD.

Between-subjects multivariate analysis of covariance (MANCOVA) will be performed to compare changes in PCBD, MDD, PTSDD, and mindfulness scores between the treatment and waiting list condition. Specifically, scores at post-treatment (in the treatment condition) and post-waiting period (in the waiting list condition) on measures tapping these phenomena will be compared, including baseline scores as covariates.

Within-subjects MANCOVA with time (baseline, 1, 12, and 24 weeks post-treatment) as the repeated measure will be performed to evaluate the short- and long-term effects of the treatment in terms of change in mean scores of PCBD, MDD, PTSD, and mindfulness. To test whether the treatment effect is mediated by changes in cognitive variables (i.e., grief cognitions, intrusive memories, rumination, and repetitive negative thinking), behavioural variables (i.e., avoidance behaviour), and self-compassion, only the scores of measures tapping these constructs that show the strongest association (based on univariate analyses) will be added to a multiple regression model. Finally, to assess the potential change at micro-level in repetitive negative thinking, intrusive memories and self-compassion throughout the course of the treatment a within-subjects repeated measures ANOVA with time (session 1 to session 8) as the repeated measure will be performed with mean scores of measures tapping repetitive negative thinking, intrusive memories, and self-compassion as outcome measures.

Data will be analysed according to the intention-to-treat principle. Missing data will be handled using multiple imputations. The Statistical Package for the Social Sciences will be used for the analysis. The small sample size of the pilot RCT increases the risk of type II error; the preliminary results regarding the potential effectiveness will therefore be reported with caution following the recommendations for conducting a pilot study [78].

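### Relatives of one missing person share an arm, but the between-arm MANCOVA treats them as independent, and lack of power does not justify this

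*Protocol article*

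**What the plan says.** **Allocation.** Under Procedure and randomisation: "Relatives of the same missing person will be allocated to the same study arm", "in order to prevent transfer of information". Recruitment includes snowball sampling through participants, and the article states no cap on the number of relatives per missing person. The same-arm rule itself anticipates families with more than one participant.

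**Analysis.** Under Data analyses, the primary analysis is: "Within-subjects repeated measures ANOVA with time (baseline, 1, 12, and 24 weeks post-treatment) as the repeated measure will be performed". The arms are compared as follows: "Between-subjects multivariate analysis of covariance (MANCOVA) will be performed to compare changes", with baseline scores as covariates. Neither model has a term, or a standard error, for the missing person. The only error risk named there is type II.

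**Reason given.** The Discussion says: "One of the limitations of this study is the lack of power to conduct a multilevel analysis to take into account the nested structure". It then describes repeated measures within individuals, and individuals within families or other social systems linked to one missing person. The Sample size section contains no design effect.

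**The concern.** In any family with more than one participant, the unit that is randomised is the missing person, not the participant. Two relatives in the same arm who share a loss tend to carry less information than two unrelated participants. An analysis that counts them as independent claims precision that the design does not supply.

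Power is therefore the wrong argument. Leaving the nesting out does not recover power. It lowers the bar for rejection, and part of the apparent gain is excess false positives. The article warns readers about type II error only, whereas this choice adds type I error. What is at stake is the p-values and intervals of the only randomised comparison, and the information that the pilot is meant to hand on to a larger trial.

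**Working it through.** **Inputs from the article:** 15 + 15 participants, 1:1 allocation, relatives of one missing person in the same arm, α = 0.05, 24 evaluable for the four-occasion ANOVA, correlation 0.50, 80% power, 19% drop-out.

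**Assumptions (not in the article):** number of relatives per missing person *m*; ICC 0.1, 0.3, 0.5; f = 0.25 for the unquantified medium effect.

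**1. The plan's own figure.** λ = f²·N·4/(1 − ρ) = 0.0625 × 24 × 4/0.5 = 12, with 3 and 69 degrees of freedom, gives power 0.817 (0.797 at N = 23). So 24 is reproduced, as a figure for 24 independent participants.

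**2. Design effect.** DE = 1 + (m − 1)·ICC. The true standard error is √DE times the unadjusted one, and the actual level is about 2·[1 − Φ(1.96/√DE)].
- Pairs, ICC 0.3: DE = 1.3, √DE = 1.14, 1.96/1.14 = 1.72, level 8.6%. The 30 participants count as 30/1.3 = 23.
- Triples, ICC 0.3: DE = 1.6, √DE = 1.265, 1.96/1.265 = 1.55, level 12.1%.
- All singletons: DE = 1, level 5%.

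**3. Between-arm simulation under the null.** Baseline-adjusted ANCOVA of one outcome, 30 participants, whole families in one arm, 10,000 replicates. It is a univariate stand-in; the four-outcome MANCOVA itself was not simulated.

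| Families per arm | ICC 0.1 | ICC 0.3 | ICC 0.5 |
|---|---|---|---|
| 15 singles | 5.2% | 4.9% | 4.9% |
| 9 singles, 3 pairs | 5.7% | 6.3% | 7.5% |
| 7 pairs, 1 single | 6.0% | 8.3% | 10.6% |
| 5 triples | 7.2% | 12.3% | 17.9% |

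**4. Within-group ANOVA under the null.** 24 participants, four occasions, with occasion-specific deviations shared within families, so that relatives' changes correlate.

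| Families | ICC 0.1 | ICC 0.3 | ICC 0.5 |
|---|---|---|---|
| 14 singles, 5 pairs | 5.2% | 7.3% | 9.4% |
| 12 pairs | 6.9% | 11.5% | 15.1% |
| 8 triples | 8.9% | 18.0% | 28.7% |

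If relatives share only their overall level, that level cancels from every within-person change. With 8 triples and ICC 0.5 the test then rejects in 4.9% of trials.

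A repeat of both tables with 100,000 replicates moved no cell by more than 1 percentage point. The largest shift was 12 pairs at ICC 0.5, from 15.1% to 16.1%.

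**5. Which remedy reaches which test.** In balanced data, random intercepts for family and participant absorb level and leave the time test as it was. In 12 simulated datasets (12 pairs, shared occasion deviations, ICC 0.3), the time F from that model equalled the ANOVA F to within 0.001 every time. Between arms, a family random intercept with cluster-based degrees of freedom brought the level back to about 3 to 6%.

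**The case against.** The other side has a good deal to say. The article discloses the nesting as a limitation, calls the study a pilot, and promises cautious reporting and later verification. The arm comparison is a secondary objective. No family sizes are given, and if almost every missing person contributes one participant, nothing changes. The all-pairs and all-triples rows are extreme compositions. All of this stands and limits the consequence. It does not make the power argument valid, and disclosure does not correct a p-value. Nor is this a detail left to an unseen analysis plan, because the article itself says the nesting will not be modelled and why.

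Two stronger readings are tempting.

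- **A reader might infer that the primary analysis is anti-conservative as well.** The article does not support that without a condition. A shared family level cancels, and inflation needs correlated change. Such correlation is plausible, since relatives share the case and any news of it, but the article gives no evidence on it.
- **A reader might infer that the same-arm rule biases the comparison**, because a relative who joins after the family's allocation could know the arm before consenting. Nobody is blinded, and no rule closes a family before allocation. But recruitment, including snowballing, is to the survey study; invitees need not be relatives of the same missing person; eligibility passes through questionnaires and an independent interviewer; an independent researcher randomises; and waiting-list participants are treated later. Nothing says that relatives join late or learn their arm first. This is a possibility, not a shown bias.

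**Conclusion.** The point holds for the between-arm comparison. With relatives allocated together and a positive within-family correlation, the unadjusted analysis understates the standard error and exceeds its nominal 5% level. For 30 participants and ICC 0.1 to 0.5, the level is about 5.6 to 7.5% with a few pairs, 6 to 11% with mostly pairs and 7 to 18% with all triples. It stays at 5% if nearly all are singletons. These are ranges under assumed ICCs and family sizes, for one outcome at a time, and the article does not allow a narrower statement.

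For the primary within-group ANOVA the point is conditional: about 5 to 9% with 14 singles and 5 pairs, and 7 to 16% with 12 pairs, if relatives' changes correlate; 5% if only their level is shared. The repeated-measures layer of the nesting is already handled by the ANOVA. Only the family layer is left out.

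It should be fixed, because the stated reason is wrong and the remedy is cheap. It is not critical, because the directly affected comparison is secondary and the trial is a pilot.

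**What to change.** - **Between-arm comparison:** add a random intercept for the missing person with Kenward-Roger or Satterthwaite degrees of freedom, or keep the mean model and use bias-corrected cluster-robust standard errors by missing person.
- **Within-group analyses:** use small-sample cluster-robust standard errors by missing person, or add a family-by-time term. Random intercepts alone do not change the time test.
- **Fallback:** if the model does not converge, analyse family means or one index relative per missing person as a sensitivity analysis.
- **Discussion:** replace the lack-of-power rationale with a statement that tests ignoring the family level risk excess type I error.
- **Reporting:** give the number of relatives per missing person and the estimated ICC, which the later trial will need.
- **Optional:** if any relative enrols after the family's allocation, repeat the between-arm comparison without that relative.

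The cost is somewhat wider intervals. If the MANCOVA is replaced, there are separate models for the four outcomes instead of one multivariate test, so multiplicity across outcomes has to be addressed. No change to recruitment, allocation or data collection is needed, beyond recording which participants belong to the same missing person.

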### Trial status

Recruitment of participants was started in January 2015 and will continue until July 1, 2016.

## Abbreviations

CBT: cognitive behavioural therapy
DSM-5: Fifth Edition of the Diagnostic and Statistical Manual of Mental Disorders
MDD: major depressive disorder
PCBD: persistent complex bereavement disorder
PTSD: post-traumatic stress disorder
RCT: randomised controlled trial
